### Randomization and experimental design

Sixty post-bariatric patients will be randomized through a random code generator software (www.randomization.com) at a ratio of 1:1 into two groups: (a) intervention group—that will perform a supervised RT program for 6 months—or (b) non-exercised control group—that will receive the standard clinical follow-up and shall not change their physical activity behavior. All patients will be followed by a multidisciplinary team (compose of endocrinologists, nutritionists, and physical educators) with expertise in post-bariatric patients, following the clinical practice guidelines [29]. Once the study is completed, for ethical reasons, the exercised control group will be invited to carry out the same RT program. Usual clinical care will be maintained for all patients following completion of the trial at our outpatients’ care unit.

The participants will visit our lab four times for data collection before and after 6 months post-intervention, with at least 24- to 48-h intervals between visits, as shown in Fig. 2. All assessments will be held in the morning between 7 and 11:00 am, in a quiet temperature-controlled environment (21–23 °C). The participants will be instructed to fast for 8 h for blood sample collections and vascular measures (at visit 2). The primary outcomes will be muscle mass and strength, bone metabolism biomarkers, BMD, and bone microarchitecture. The secondary outcomes will be anthropometry, hemodynamic measurement, metabolic/cardiovascular risk factors, health-related QoL, and endothelial function.

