### Recruitment and eligibility criteria

We will approach patients subjected exclusively to RYGB in regular clinical follow-up, aging 18 to 50 years and after at least 12 months from surgery. Our outpatients’ care unit follows at least 180 patients subjected to a bariatric procedure each year. Considering the inclusion and exclusion criteria, we expect to recruit 40 to 60 patients. The exclusion criteria will include regular physical exercise (≥ 3 days/week during 30 min) in the last 6 months; smoking; alcoholism; pregnancy; diagnosis or evidence of any cardiovascular; respiratory, neurological, infectious, endocrine, or musculoskeletal impairments that limit physical exercise; and or being in the use of any hormonal replacement therapy or medications that influence bone metabolism. Those who start some physical exercise program during the study, or with excess weight loss (EWL) < 50% (considered as primary non-responders) [28], or being in the use of drugs that interfere with weight, or who have performed a revisional bariatric surgery will also be excluded.

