#### Handgrip strength test and sarcopenia cutoff points

Isometric maximal handgrip strength will be measured by hand dynamometer TSD121C Hand Dynamometer (Biopac Systems, Inc., CA, USA) with the patients seated in a chair, with elbows flexed and the forearm in supinated position (dominant arm). The patients will perform three attempts of 5 s interspersed with 2-min intervals, and the highest value will be recorded as a result.

Sarcopenia will be detected by cutoff points of low muscle strength and low muscle mass, assessed by the handgrip test and ASM measurement, respectively, defining it as probable or confirmed sarcopenia, according to current consensus [19]. Sarcopenia cutoff points for low muscle strength from Dodds et al. [32] and low muscle mass from Baumgartner et al. [33] will be applied, considering the ratio between ASM by DXA and height squared (ASM index) of 5.45 and 7.26 kg/m^2^ and a handgrip strength of 16 and 27 kg for women and men, respectively.

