### Sample size calculation and statistical analysis

In this study, it will be used a similar sample size previously used in a trial which provides 90% detection power between-group differences of BMD, with a significance level of 0.05 [54]. Descriptive analysis will consist of means and SD for continuous variables and percentages for categorical variables. Data normality will be tested by the Shapiro-Wilk test with the results expressed as mean ± SD or percentage, whenever appropriate. Baseline variables will be compared between the groups using either the Student *t*-test or chi-squared test. To compare dependent variables, a two-way ANOVA will be used considering group (intervention and non-exercised control groups) and time points (pre and post-intervention), followed by the Bonferroni post hoc test, in case of significant *F* ratios. An intention-to-treat analysis will be conducted, i.e., all participants, regardless of adherence to the intervention, will be included in the final analysis. No additional analyses are planned for the study. All calculations will be performed using the GraphPad™ software (version 6.0, La Jolla, CA, USA), and the significance level will be set at *P* ≤ 0.05.

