## Discussion

Physical exercise programs could positively influence bone and muscle health in several clinical populations [21–24, 56, 57], including post-bariatric patients [26]. This benefit is relevant, given the relationship between osteoporosis and sarcopenia vs. disability and mortality [19, 58]. On the other hand, available evidence suggests that several surgical results are worsened by lack of physical exercise leading to the return of obesity-related comorbidities and regression in QoL [47, 59]. In this context, defining which exercise strategy better suits this population and which one is more effective in improving these outcomes is relevant.

Previous studies have demonstrated this prospect, but the assessment of all these outcomes is needed in a large randomized controlled trial [60–62]. In summary, the effects of RT on clinical and health consequences of post-bariatric patients are not consensual, probably due to the methodological limitations of the current literature. In general, trials that applied isolated RT programs used various experimental designs, including training variables (frequency, intensity, duration, volume, or progression), the sample used (small sample size, only females or both sexes, or participants of different ages and clinical conditions), the nutritional status (supplementation use or not), and also the start period of the RT program after surgery [26]. Moreover, even considering RT the most effective exercise used to preserve skeletal integrity [54], data on the literature concerning the influence of an isolated RT program on bone adaptations and bone turnover in post-bariatric patients is scarce.

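### Neither the described allocation nor the covariate-free analysis accounts for time since surgery or sex, which can cost precision and leaves any chance imbalance uncorrected

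*Protocol article*

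**What the plan says.** All references are to the protocol article.

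- **Entry (Recruitment and eligibility criteria).** Patients are "aging 18 to 50 years and after at least 12 months from surgery". There is no upper limit on time since surgery and no restriction by sex. The sarcopenia section sets "a handgrip strength of 16 and 27 kg for women and men, respectively", so both sexes are expected.
- **Numbers.** The randomisation section fixes 60 patients, while the recruitment section says "we expect to recruit 40 to 60 patients".
- **Allocation (Randomization and experimental design).** "Sixty post-bariatric patients will be randomized through a random code generator software (www.randomization.com) at a ratio of 1:1 into two groups". No strata, blocks or minimisation factors are named.
- **Analysis (Sample size calculation and statistical analysis).** "a two-way ANOVA will be used considering group (intervention and non-exercised control groups) and time points (pre and post-intervention", with Bonferroni post hoc tests. Baseline variables are compared between arms by t-test or chi-squared test. No covariate is named, and the section states that nothing beyond this is planned.
- **Sample size (same section).** The number is borrowed: "it will be used a similar sample size previously used in a trial". The earlier trial is credited with 90% power for a BMD difference between arms at the 0.05 level. No difference or SD is given.

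**The concern.** The outcome of interest is change over 6 months. Patients one year and many years after bypass may not be on the same course for bone and muscle, and women and men may differ too. The article treats both as relevant when it explains why earlier trials disagree: it lists the sex mix of the samples "and also the start period of the RT program after surgery".

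Measuring before and after removes differences in baseline level. It does not remove differences in the 6-month trajectory. If the arms happen to differ on a factor that predicts trajectory, the unadjusted difference in change carries that imbalance. The baseline tests might reveal it, but nothing in the stated analysis corrects it. With 20 to 30 patients per arm, such imbalances are not rare. At stake is some precision on the bone and muscle outcomes, and an awkward interpretation if the draw is unlucky.

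**Working it through.** **The plan's own figure.** The 90% power cannot be reproduced, because no difference or SD is stated. Back-solving for two means, two-sided 0.05 (sidedness is an assumption), d = (1.96 + 1.28) × √(2/n):
- n = 30 per arm: d = 3.24 × 0.258 = 0.84 SD
- n = 20 per arm: d = 3.24 × 0.316 = 1.03 SD

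Power is therefore well below 90% for smaller effects, and precision matters there.

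**Chance imbalance on a two-level factor.** Take N patients in two equal arms of n, of whom K have the factor. With k of them in one arm, the difference in proportions is |2k − K|/n, and k is hypergeometric. At N = 60, a gap of 20 points means |2k − K| ≥ 0.20 × 30 = 6. For K = 12 that is k ≤ 3 or k ≥ 9. At N = 40 the condition is |2k − K| ≥ 4.

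| Prevalence of factor | N = 60 | N = 40 |
|---|---|---|
| 20% | 0.104 | 0.235 |
| 30% | 0.158 | 0.301 |
| 50% | 0.196 | 0.343 |

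The prevalences are assumptions. The article gives neither the expected sex mix nor the distribution of time since surgery.

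**Chance imbalance on a continuous factor.** The standardised mean difference (SMD) between arms has SE √(2/n).
- |SMD| ≥ 0.25: 33% of randomisations at N = 60, 43% at N = 40
- |SMD| ≥ 0.5: 5.3% at N = 60, 11.4% at N = 40

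**Consequence for the comparison.** Read as a repeated-measures analysis, the group-by-time interaction with two time points is the two-sample test of change. Simulation: 30 per arm, 20,000 runs per scenario, one covariate with correlation rho to the 6-month change, unadjusted t-test against ANCOVA. Rho and the true effect are assumptions.

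| rho | Power at 0.5 SD, unadjusted → adjusted | Power at 0.3 SD, unadjusted → adjusted |
|---|---|---|
| 0 | 0.481 → 0.475 | 0.208 → 0.206 |
| 0.2 | 0.474 → 0.485 | 0.208 → 0.211 |
| 0.3 | 0.476 → 0.504 | 0.208 → 0.222 |
| 0.5 | 0.478 → 0.588 | 0.211 → 0.256 |

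At 0.5 SD the gain is about 1 point (rho 0.2), 3 points (rho 0.3) and 11 points (rho 0.5). With a useless covariate the loss is under 1 point.

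With no true effect, the unadjusted rejection rate over all draws is 0.045 to 0.051, so overall type I error is intact. Within the 5.3% of draws with |SMD| ≥ 0.5, the unadjusted estimate shifts by about 0.12, 0.18 and 0.30 SD for rho 0.2, 0.3 and 0.5. The false-positive rate in those draws is about 6%, 9% and 18%.

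**The case against.** Four points on the other side deserve weight.

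1. **Stratification may exist.** The article names a generator and a ratio; it does not say the list is simple or unstratified. Strata and blocks are details an article often leaves to a full protocol, which is not shown. This stands, and the allocation part of the fix is conditional on it. The lack of covariates in the analysis is different: the model is stated, and further analyses are ruled out.
2. **Unstratified randomisation is valid.** A reader might infer that the trial is biased, or that its error rate is inflated. Neither is so: chance imbalance is part of the sampling error that the test already allows for. This stands in full.
3. **The prognostic link is not documented.** A reader might take the Background to show bone loss that continues through the eligible period. It reports reduced BMD, muscle loss and weight regain after surgery, but gives no time course beyond 12 months. Nor does it say that sex alters 6-month change. Eligibility also narrows the sample by procedure, weight response, revisional surgery and medication. This stands, so the harm can be given only as a range.
4. **The Discussion is about other trials.** A reader might conclude that this trial repeats the fault it finds in earlier work. The passage mainly describes differences between trials, not missing stratification within one. It shows that the authors regard these factors as relevant, and no more.

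What survives is that two plausible predictors, both known at screening, are used neither in the allocation as described nor in the analysis as fixed.

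**Conclusion.** The point holds as a matter of precision and of an uncorrected chance imbalance. It is not a bias or a type I error problem. A 20-point imbalance on a two-level factor is a 1-in-10 to 1-in-5 event at 60 patients, and roughly 1-in-4 to 1-in-3 at 40.

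The cost is small if the factors predict 6-month change weakly and appreciable only if they predict it strongly. A larger distortion of 0.12 to 0.30 SD arises only in the roughly 5% of draws at 60 patients with an SMD of at least 0.5, and it can go in either direction. It would therefore be wrong to say that the design is likely to hide or create an effect.

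These results assume equal arms, prevalences of 20% to 50%, rho of 0.2 to 0.5 and true effects of 0.3 to 0.5 SD; none of the last three is given in the article. The change is worth making because it is cheap and, on the allocation side, possible only before patients are randomised. The article's Trial status says recruitment had not begun.

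**What to change.** **Analysis.** Replace the covariate-free ANOVA with a prespecified between-arm comparison of the 6-month value, adjusted for the baseline value of that outcome, time since surgery (continuous) and sex.

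**Allocation.** If the full protocol already stratifies, name the factors in the public text and include them in the model. If it does not, generate blocked 1:1 lists by time since surgery, with one cut-off fixed before recruitment, and also by sex if enough men are expected. Carry the same factors into the model. With 40 to 60 patients, use no more than these two factors.

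**Cost.** The analysis uses a few degrees of freedom, about 1 point of power if time since surgery and sex turn out not to be prognostic. Allocation needs two to four lists instead of one, with some incomplete blocks in sparse strata and a slightly more complex log. Both factors are known at screening, so no new data are needed.

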#### Biochemical parameters

##### Methodology for hemogram, glycemia, lipid profile, and blood total protein evaluations

Hemogram will be performed by automatically counting blood cells from whole blood samples. Plasma glucose levels will be determined by the colorimetric glucose oxidase method. Blood will also be collected to assess the serum insulin levels and lipid profile. Serum insulinemia will be evaluated by an electrochemiluminescent immunoassay (Elecsys Insulin Assay, Roche Diagnostics GmbH, Mannheim, Germany) through an automatic analyzer (Cobas e411; Roche Diagnostics, Munich, Germany), as previously described [34]. The serum levels of triglycerides (TG), total cholesterol (TC), high-density lipoprotein cholesterol (HDL-c), and total proteins will be assessed by colorimetric methods glycerol-phosphate oxidase/peroxidase, cholesterol oxidase/peroxidase, direct detergent, and biuret, respectively. All analyses will be performed using commercially available kits suitable for an A25 automatic analyzer (BioSystems, Barcelona, Spain). Low-density lipoprotein cholesterol (LDL-c) will be calculated using the Friedwald equation [35].

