#### High-resolution peripheral quantitative computed tomography (HR-pQCT)

Volumetric BMD and bone microarchitecture will be measured on the non-dominant distal radius and tibia using a three-dimensional HR-pQCT system (XtremeCT, Scanco Medical AG, Brüttisellen, Switzerland), as previously described [46]. The variables that will be analyzed include the following: (i) volumetric BMD for total, trabecular, and cortical regions (Tt.vBMD, Tb.vBMD, and Ct.vBMD; mg of hydroxyapatite/cm^3^); (ii) cortical thickness, calculated by dividing the cortical volume by the external bone surface (CtTh; mm); (iii) percentage of trabecular bone volume, i.e., ratio of BV to total volume (BV/TV; %); (iv) trabecular thickness (TbTh; mm); (v) trabecular number (TbN; 1/mm); (vi) trabecular separation (TbSp; mm); and (vii) SD of TbSp (TbSp 1/N SD; mm).

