#### Hemodynamic and cardiometabolic risk factors measurements

Resting blood pressure and heart rate will be assessed in the non-dominant arm by a semi-automated oscillometric device (G-TechTM BSP11, Hangzhou, Zhejiang, China) in a controlled and quiet environment after 10-min resting in a sitting position, according to the standard recommendations [49]. Cardiometabolic risk factors will be evaluated by BMI, waist circumference, blood pressure, triglycerides, HDL-c, LDL-c, total cholesterol, and fasting plasma glucose [50].

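### About 32 variables (up to 39) are co-equally primary, each tested at 0.05 with no correction across outcomes, so the chance of a false primary finding is far above 5%

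*Protocol article*

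**What the plan says.** The Abstract and the section Randomization and experimental design give the same primary set, unranked: "The primary outcomes will be muscle mass and strength, bone metabolism biomarkers, BMD, and bone microarchitecture". The section Primary outcomes measures then lists what will be measured in each domain. One example is the high-resolution peripheral CT (HR-pQCT) list, which opens with "volumetric BMD for total, trabecular, and cortical regions", adds six further indices, and applies to both radius and tibia.

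The section Sample size calculation and statistical analysis treats all outcomes alike: "To compare dependent variables, a two-way ANOVA will be used considering group" and time point, "followed by the Bonferroni post hoc test, in case of significant" F ratios, and "the significance level will be set at *P* ≤ 0.05". It names no main variable, no order of testing and no adjustment across variables, and it says that no additional analyses are planned. The 90% power claim concerns BMD only. It is taken from a cited trial, and no skeletal site, effect size or SD is given.

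**The concern.** A superiority trial needs a stated result on which its conclusion rests. Here any one of some thirty variables could serve, and each has its own 5% chance of a false positive. The Bonferroni step does not help. It follows a significant F ratio and compares group and time cells for one variable, leaving the number of variables uncorrected.

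A second, separate problem concerns 1RM. The 1RM test is used to set training loads, and the intervention arm trains for six months. A gain in 1RM would probably be real, so it is not a chance finding. Under this primary set it could still be presented as a primary success even if BMD, the only outcome with a power claim, did not differ.

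**Working it through.** **Step 1: count the primary variables** (from the subsections of Primary outcomes measures).

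| Domain | Variables | Number |
|---|---|---|
| Muscle mass | appendicular skeletal muscle mass | 1 |
| Strength | handgrip | 1 |
| Strength | 1RM | 1 if one summary value; 8 if each trained lift is analysed |
| BMD by DXA | lumbar spine, femoral neck, total femur, one-third radius | 4 |
| Bone biomarkers | P1NP, osteocalcin, BAP, sRANKL, CTX-1, PTH, vitamin D | 7 |
| HR-pQCT | (3 volumetric densities + 6 other indices) × 2 sites | 18 |

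Total: 1 + 1 + 1 + 4 + 7 + 18 = 32. With eight lifts: 32 + 7 = 39. The protocol says 1RM is attempted for each exercise, and the Intervention section lists eight. It does not say that all eight are tested or analysed separately. The count leaves out BMD Z-scores, calcium and phosphorus. It takes one test per variable, although a two-way ANOVA gives group, time and interaction F tests and the protocol does not say which one decides.

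**Step 2: chance of at least one P ≤ 0.05 when no primary variable has a true effect.** Tests are assumed two-sided. Under independence this is 1 − 0.95^m.

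- m = 32: 1 − 0.95^32 = 0.806; expected false positives 32 × 0.05 = 1.6.
- m = 39: 1 − 0.95^39 = 0.865; expected false positives 39 × 0.05 = 1.95.

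**Step 3: allow for correlation.** The documents give no correlations, so these values are assumptions. With a common correlation r, write each test statistic as Z = √r·G + √(1−r)·e, with G shared by all tests. The chance is then 1 − ∫ φ(g)·[Φ((1.96 − √r·g)/√(1−r)) − Φ((−1.96 − √r·g)/√(1−r))]^m dg.

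| r | m = 32 | m = 39 |
|---|---|---|
| 0 | 81% | 86% |
| 0.3 | 68% | 74% |
| 0.5 | 52% | 57% |
| 0.6 | 43% | 47% |
| 0.7 | 35% | 37% |

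A simulation with correlation mainly within domains (100,000 draws) gives:

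- 65–76% at within-domain 0.5 (between-domain 0 to 0.1);
- 55–66% at 0.7 (between-domain 0 to 0.1);
- 44–58% at 0.8 (between-domain 0.1 to 0.3);
- 37–48% at 0.9 (between-domain 0.1 to 0.3).

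**Step 4: what full correction would cost.** The plan's 90% power cannot be reproduced, because the effect and SD are not in the article. Working backwards with 60 patients at 1:1 (30 per arm), a two-sided t-test at 0.05 has 90% power for a difference of 0.851 SD. At that same difference:

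- Bonferroni over 32: alpha 0.05/32 = 0.00156, power about 50%.
- Bonferroni over 39: alpha 0.05/39 = 0.00128, power about 47%.

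The normal approximation (0.837 SD) gives 53% and 51%.

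**The case against.** **A statistical analysis plan may settle the success rule.** Such a plan is not shown, and testing order and adjustment are often placed there. This limits the criticism to what the article fixes. But the article itself fixes the primary set, the test and the alpha level, and rules out additional analyses. A later document would have to repair that choice.

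**Independence is implausible.** This stands. Eighteen of the variables are HR-pQCT measures from two sites, and total volumetric density overlaps with its trabecular and cortical parts. A reader might infer that a chance positive is more likely than not whatever the correlation. The documents do not support that. With equal correlation the figure drops below one half between 0.5 and 0.6. With correlation mainly within domains this happens at about 0.8 to 0.9.

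**The count is a tally.** This also stands. The protocol names domains and never lists the dependent variables to be analysed, and 39 depends on the assumption about the lifts.

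**The 1RM argument is not about chance.** Agreed. It concerns a true but uninformative positive and adds nothing to the percentages above.

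**Glucose and lipids.** Under the primary heading stands a subsection titled "Methodology for hemogram, glycemia, lipid profile, and blood total protein evaluations", and a reader might add these tests to the primary family. The cardiometabolic subsection under secondary outcomes lists "triglycerides, HDL-c, LDL-c, total cholesterol, and fasting plasma glucose", and the experimental design section also makes metabolic risk factors secondary. This is a matter of heading layout, and they are not counted here.

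**Conclusion.** The point holds in conditional form. As written, the plan has about 32 co-equal primary variables and no error control across them. If none truly responds, the chance of a false primary finding runs from 35–37% (common correlation 0.7) to 81–86% (independence). Even 35% is seven times the nominal 5%. The result rests on two-sided tests, one test per variable, the tally above and assumed correlations. It does not depend on the sample size, which the article gives no means to confirm or refute. The 1RM problem is a separate weakness of the same primary set.

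**What to change.** Before recruitment, which the Trial status section says has not begun:

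- Name one primary outcome and its deciding test, the group-by-time interaction. BMD at one stated site is the natural choice, because the power claim is for BMD.
- Make the other muscle, strength, biomarker and HR-pQCT variables secondary or exploratory, and state that the trial's conclusion rests on the single primary.
- Place the hemogram, glucose and lipid methods outside the primary heading.

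If the investigators prefer one primary per domain, they should name one variable in each, use a fixed-sequence order or Holm across those few, and restate the power. With five (muscle mass and strength taken separately), the strictest Holm step is 0.05/5 = 0.01, where the 90% becomes about 73% by the same t-test calculation. Bonferroni over the whole list is the expensive route, for the reason shown in the working.

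The cost is a wording amendment, with the trial registration aligned if it carries the same primary set (that record is not at hand). The downside is that fewer outcomes can be claimed as confirmatory.
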